### Analyses WP6

A detailed study and analysis protocol will be published at OSF prior to the statistical analyses. The data analysis will follow the hierarchical clustered structure of the study (patients nested within practices). Logistic mixed-effects regression models will be applied to analyse the primary outcome, with a fixed effect for the group (intervention versus control) and a random intercept for the practices. The same model will be used on the secondary outcomes. Models will be adjusted for pre-defined potential confounders: patients’ age, sex, education, level of PA, and BMI. All patients will be included in an intention-to-treat analysis. Based on experiences from another cRCT [52], missing data on the primary outcome is assumed to be minimal as data will be collected through face-to-face interviews. However, multiple imputation will be applied to impute missing data if needed.

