## Phase II) Piloting of the intervention study and of the main evaluation study

### WP5: Pilot study

Based on preliminary work of the study team [22] and as recommended according to the MRC framework [31], a feasibility study testing the practicality of the planned evaluation study (WP6) is not considered necessary. Instead, a pilot study will be carried out to evaluate implementation outcomes, including the training of GP peer trainers, recruitment and randomisation processes, content and schedule of the training, materials, methods of data collection among patients and GPs including pre-tests of the study questionnaire and potential need for sample size adjustment. The pilot study will essentially function as a “scale model” of one study cycle of the planned pragmatic, two-arm, clustered randomised controlled trial (cRCT). For each study cycle, ten GP practices will be randomised (1:1) into either the intervention or control group. A study cycle is defined as a period of 5 weeks of face-to-face, practice-based data collection in people with IHD immediately following consultation with GPs who have been trained (intervention group, *n* = 5 practices) and a period of 5 weeks of face-to-face data collection in people with IHD immediately after consultation with GPs who have not been trained (control group, n = 5 practices). Per practice, approximately twelve people with IHD will be recruited, resulting in a pilot sample of 120 people with IHD.

A process evaluation with semi-structured, problem-centred individual interviews with GPs of the pilot study and with their patients with IHD who received PA advice will also be conducted. The aim is to understand: A) to what extent training contents could be implemented into practice, which factors facilitated or hampered the transfer, and how GPs experienced the delivery of very brief PA advice, and B) patients’ experiences with received advice, and their met and unmet needs. Experiences with the study procedures will be explored in both groups. Approximately six to eight interviews per group are expected to be sufficient. Data collection will continue until reaching data saturation [42] (for methodological details see WP2). Based on the insights gained from these interviews, study processes and the training manual will be further refined.

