**Fig. 2 Fig2:**
[figure not shown]
Study flow of the planned cluster randomised controlled trial (O = no training). A study cycle consists of 10 weeks of data collection: 5 weeks patients of “control” and 5 weeks in patients of “intervention” general practitioners (GPs). In total there will be five cycles resulting in 50 practices (25 intervention and 25 control practices)

As described in WP1, we calculate with an estimate of 20% of patients who report the receipt of brief PA advice during their GP visit without the GP having been trained. Another study showed that a brief single-session GP training can increase patient-reported rates of GP-delivered stop-smoking advice by 20%-points on average [52]. Training GPs to deliver PA advice might be more challenging, e.g., because PA recommendations are more complex than simple advice on smoking cessation methods. Training on PA advice is thus declared to have a clinically relevant effect if higher rates of delivered PA advice of at least 13%-points can be achieved in the intervention group (33%) as compared to the control group (20%), corresponding to an odds ratio of 1.97. Sample size calculation is based on the standard χ2-test in a four-fold-table and a multiplicative correction (= 1 + 0.05*(12–1) = 1.55, i.e., assuming an intraclass correlation coefficient of 0.05 and twelve IHD patients/practice) by the design effect to account for clustering. Including a total of 600 people with IHD in 50 practices (25 per study arm) will yield a power of at least 85% in the primary analysis of the intervention effect in a logistic regression model with a random intercept effect accounting for the nested design, while adjusting for patient and practice characteristics.

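### The WP6 primary model leaves out study cycle, apparently the randomisation block, and its covariate list disagrees with the one in the sample-size paragraph

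*Protocol article*

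**What the plan says.** All references are to the protocol article.

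- **Randomisation.** Section WP5: Pilot study, which presents the pilot as a miniature of one cycle of the main trial: "For each study cycle, ten GP practices will be randomised (1:1) into either the intervention or control group", with five practices per arm.
- **Main trial.** Section WP6: Main evaluation study, Fig. 2 caption: "In total there will be five cycles resulting in 50 practices (25 intervention and 25 control practices". The WP6 text itself states 1:1 randomisation but does not restate that it is done within cycle.
- **Primary model.** Section Analyses WP6: a logistic mixed model "with a fixed effect for the group (intervention versus control) and a random intercept for the practices", with the same model for the secondary outcomes.
- **Covariates, analysis section.** "Models will be adjusted for pre-defined potential confounders: patients’ age, sex, education, level of PA, and BMI". All five are patient-level.
- **Covariates, sample-size paragraph of WP6.** Power is stated for a random-intercept logistic model "while adjusting for patient and practice characteristics".
- **Deferred detail.** WP6 is described only briefly because details may change after the pilot, and a fuller analysis protocol is to appear on OSF before analysis.

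**The concern.** Two things do not line up.

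First, if allocation is balanced 5:5 within each cycle, differences between cycles cancel out of the treatment comparison by design. A model without cycle does not know this. It counts between-cycle variation as practice-level noise, so the standard error is larger than the true sampling variability of the estimate. Cycles could plausibly differ: each has its own practices and calendar period, and at ten weeks each, five run back to back would span 50 weeks (the article does not give the spacing). WP6 itself keeps the two arms' data-collection periods close together because patient flow fluctuates.

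Second, the sample-size paragraph and the analysis section describe different covariate sets for the same primary model. No practice characteristic is named as a covariate anywhere in the article, and the practice random intercept does not fill that role, since the sample-size paragraph mentions it separately.

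At stake are some precision and an unambiguous pre-specified model. The validity of the trial is not in question.

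**Working it through.** **Step 1. The plan's own figures.** The inputs, from the WP6 sample-size paragraph, are 20% versus 33%, ICC 0.05, 12 patients per practice and 300 patients per arm. Alpha is not stated; two-sided 0.05 is assumed here.

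- Design effect: 1 + 0.05 × (12 − 1) = 1.55. Agrees.
- Odds ratio: (0.33/0.67) / (0.20/0.80) = 1.97. Agrees.
- Effective size per arm: 300 / 1.55 = 193.5.
- Power of the χ² test: Φ{[0.13 × √193.5 − 1.96 × √(2 × 0.265 × 0.735)] / √(0.20 × 0.80 + 0.33 × 0.67)} = Φ{(1.809 − 1.223) / 0.617} = 82.8%. The plan states at least 85%.

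The gap depends on the unstated alpha and on the variant used (83.4% with unpooled variance, 89.7% one-sided), and it is a separate matter. What counts here is that neither a covariate nor a cycle component enters this calculation. The stated power is therefore unaffected by which covariates are listed.

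**Step 2. Mechanism.** In units of p(1 − p), the variance of a practice mean is 1.55/12 = 0.1292. Suppose 30% of the ICC lies between cycles, that is 0.015. The variance relevant to a comparison balanced within cycles is then 0.1292 − 0.015 = 0.1142. A model without cycle uses 48 residual degrees of freedom, 4 of which carry cycle differences. With ten practices per cycle, its expected residual variance is 0.1142 + (4 × 10/48) × 0.015 = 0.1267. The standard error is overstated by √(0.1267/0.1142) = 1.05, about 5%. The error is in the conservative direction.

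**Step 3. Simulation.** The layout was 5 cycles × (5 + 5) practices × 12 patients, with total between-practice variance held at an ICC of about 0.05 and 20,000 replicates per setting. Practice proportions were compared by a t-test without cycle (48 df) and with cycle (44 df), two-sided 0.05. The cycle share is assumed.

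| Cycle share of between-practice variance | Type I error, without → with cycle | Power, without → with cycle | Gain in power (from unrounded values) |
|---|---|---|---|
| 0 | 5.1% → 5.1% | 81.4% → 81.1% | −0.3 |
| 10% | 4.7% → 4.9% | 81.8% → 82.6% | +0.7 |
| 20% | 4.4% → 5.0% | 82.8% → 84.4% | +1.6 |
| 30% | 4.2% → 5.2% | 83.2% → 85.6% | +2.4 |
| 50% | 3.8% → 5.2% | 84.9% → 88.6% | +3.8 |

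The Monte Carlo standard error of a 5% rate is √(0.05 × 0.95/20,000) = 0.15 points, so the values with the cycle term are compatible with 5%. A second simulation of the same layout at a 30% share gave type I error 4.0% → 5.0% and power 83.0% → 85.5%, in close agreement.

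**Step 4. The covariate statements side by side.** The sample-size paragraph names patient and practice characteristics. The analysis section gives a pre-defined list of age, sex, education, physical activity level and BMI. One model cannot match both.

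**The case against.** The strongest reply is that this is a condensed article. WP6 is openly provisional, an OSF analysis protocol is promised, and nothing rules out a cycle term there. That carries weight for the cycle term, which the later document could add. It carries less for the covariates, because the article already commits to two different sets and no later document can agree with both.

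Other points that stand:

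- Blocking by cycle in WP6 is inferred. The explicit wording is in the pilot section; the main trial's description only fits it.
- A reader might infer that the omission costs power against the plan. The documents do not support that. The plan's calculation has no cycle component, and with the total ICC fixed, power without the term rises with the cycle share (81.4% to 84.9% in the table). What is lost is a possible gain.
- A reader might infer that the covariate mismatch undermines the power figure. It does not: that figure comes from a χ² test with a design effect and uses no covariates.
- A reader might expect a cycle term to deal with the calendar difference between arms. It cannot, because the two five-week periods within a cycle are sequential.
- The simulation compares practice proportions; it does not fit the planned patient-level logistic mixed model with covariates. It shows direction and approximate size only.

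**Conclusion.** The point holds in a limited form. The primary model omits what appears to be the randomisation block. If advice rates differ between cycles, the result is mild conservatism and forgone precision: type I error of about 5.1% down to 3.8% in place of about 5%, and 0 to about 4 points of power not gained, for an assumed cycle share of 0 to 50% at a total ICC of 0.05. If cycles do not differ, nothing is lost by the omission. The treatment estimate is not biased on this account and false positives are not inflated. The size rests wholly on the assumed cycle share, on 5:5 allocation within cycles carrying over from the pilot, and on two-sided alpha 0.05.

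The covariate disagreement is certain on the face of the text. It is a matter of making the pre-specified model unambiguous and does not bear on the stated power.

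**What to change.** 1. State in WP6 whether randomisation is stratified by study cycle.
2. In Analyses WP6, add study cycle (five levels) as a fixed effect to the primary and secondary models. The cost is 4 of 48 practice-level degrees of freedom and at most about 0.3 points of power if cycles do not differ. Cycle is known from the schedule, so no data collection is needed.
3. Make the two covariate statements agree. Either delete the reference to practice characteristics from the sample-size paragraph, which costs nothing, or pre-specify practice covariates that WP6 will actually record. The article does not show that any are recorded, so the second option may need an added data item.

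WP6 had not started when the article was submitted. These edits can go into the OSF analysis protocol; making them before outcome data exist avoids any question of post-hoc covariate choice.

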### Current status

At the time of submission of this protocol, WP 6 hat not started yet.

## Discussion

PA has been demonstrated to have substantial secondary preventive effects in IHD [8, 9]. Despite clinical guidelines advocating for the delivery of brief advice on PA in the primary care of people with IHD [12], this recommendation seems to be insufficiently implemented [26], often due to a lack of training [27]. While international guidelines recommend training GPs to provide such advice [11, 19], evidence is still lacking on whether brief training can effectively improve the proportions and quality of GP-delivered PA advice in routine healthcare. The *OptiCor* project intends to bridge this gap. This study protocol describes the systematic development and evaluation of a complex intervention for optimising the treatment of people with IHD by training GPs to effectively and efficiently deliver very brief advice on PA.

A strength of the study is the use of the MRC framework [31] and its core elements to systematically develop and evaluate the intervention. The development follows the COM-B behavioural model [35], and the BCT [28] will be used to describe the active elements of the training. This will make the intervention replicable in its design and results. In addition, the systematic inclusion of GPs and people with IHD (including patient representatives) in the study design and development of the training, as well as the pragmatic evaluation approach with relatively unselected patients and under real-world practice conditions, will strengthen the external validity of the results and may provide methodological and procedural data for future implementation studies.

The study also has limitations. Firstly, no medium- or long-term follow-up of patient or GP behaviour is planned for the cRCT for practical reasons. Thus, only short-term effects of the intervention on the GPs’ behaviour can be determined. Nevertheless, the study shows whether training for GPs has the potential to increase the proportions of GP-delivered PA advice in general. If this proves to be true, strategies can be devised (e.g., blended-learning refresher modules) to ensure sustainable training effects. Secondly, only GPs and people with IHD from one federal state (NRW) will be included in the study, limiting the study’s generalisability across Germany. However, NRW is the most populous German federal state, with a broad socioeconomic variability, and the recruitment will be conducted across urban and rural areas to ensure diversity. Thirdly, a selection bias could occur if particularly engaged or interested GPs and people with IHD are more likely to participate in the respective studies. In WP1, non-response analyses will be conducted and the application of multiple imputation methods will be considered. In WP2, one strategy to mitigate potential selection bias is to recruit complete GP quality circles for the focus groups. GPs in these quality circles are assumed to have different positions and motivations with regard to PA advice. In WP5 and WP6, randomisation should ensure equal distribution of such attitudes over both study arms. Nevertheless, a potential selection bias of GPs with a particular interest in lifestyle counselling or PA cannot be completely avoided. We will further explore and apply strategies to minimise selection bias by recruiting less motivated GPs (e.g., by “cold calling”). Lastly, as no physiological IHD markers or PA levels of patients will be investigated, effects of GPs' advice on the PA levels of people with IHD or on IHD progression will remain unclear for this study. Nevertheless, as reported in the background of this protocol, evidence is strong that GP advice increases PA levels at least in the medium term, and that regular PA improves the clinical outcomes of IHD [14–16].

## Conclusion

If the systematically developed training increases the frequency and quality of GP-delivered PA advice for secondary prevention of IHD, it could provide a low-threshold and sustainable strategy for implementing PA guideline recommendations for the management of IHD in general practice. The short duration of the training could further facilitate widespread implementation in the continuing education of GPs. It would also be conceivable to transfer the training on the delivery of very brief advice on PA to disease management of other chronic conditions (e.g., arterial hypertension, type 2 diabetes mellitus, depression), as well as to other healthcare settings (e.g., hospital, other specialists).

## Data Availability

The data which will be collected with this study are third-party data and will be available to researchers on reasonable request by contacting the principal investigator ([contact]). All proposals requesting data access will need to specify how it is planned to use the data, and all proposals will need approval of the study team before data release.

## Abbreviations

IHD: Chronic ischemic heart disease
PA: Physical activity
GP: General practitioner
cRCT: Cluster randomised controlled trial
WP: Work package
DRKS: German Clinical Trials Register
WHO: World Health Organization
DMP: Disease Management Program
NNT: Number needed to treat
NICE: National Institute for Care Excellence
3As: Ask/Assess, advice, assist
MRC framework: Medical research council framework
BMI: Body mass index
CAPI: Computer-assisted personal interview
OSF: Open Science Framework
NRW: North Rhine Westphalia
BCT: Behaviour change taxonomy
DCE: Discrete choice experiment
